#### Clinical outcomes

Analgesic use; duration of operation (minutes) and complication rates; conversion rates; infection rates (intra-abdominal and wound); related hospital re-admission rates up to six weeks; reoperation rates and port-site hernia up to six weeks.

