### Concealment of group allocation to participants

The feasibility of concealing group allocation from the participants and the ward staff will be investigated. Although blinding in the theatre is not possible given this is a surgical trial, participants will not be informed after their surgery of the procedure actually carried out. Blinding of participants will be attempted by using three hypoallergenic dressings applied at the umbilicus, in the left lower quadrant and hypogastrium unless conversion to open abdomen is required.

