### Sample size

As there were no published RCTs comparing single port laparoscopic appendicectomy with standard three-port laparoscopic appendicectomy when the study was designed [8], a formal sample size calculation based upon previous data was not possible. A sample of 80 participants recruited is anticipated over the seven-month recruitment phase. Adopting a 5% two-sided significance level, this would allow an effect size (Cohen’s d) of 0.65 to be detected with 80% power for patient reported measures, such as the Body Image Questionnaire [19]. Binary feasibility measures are likely to be estimated with a (one-group) confidence interval of between 10 and 20% depending upon the corresponding event rate [19].

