### Subsequent tasks

Following formal trial entry -

The Study Office will:

i. Inform the participant’s GP (by letter enclosing information about SCARLESS and Study Office contact details).

ii. Process the pain Numerical Rating Scale (NRS) seven-day diary and the six-week participant questionnaire.

iii. Collect the feasibility measures.

The consultant or team member will:

i. Provide the original signed consent form to the Study Office and file the Hospital Copy of the form in the hospital notes along with information about SCARLESS.

ii. Inform the ward and theatre staff as appropriate of the participant’s study participation and intervention allocation.

iii. Complete case report forms (CRFs) as appropriate and either enter the data directly onto the SCARLESS website or forward the hard copies of the CRFs to the co-ordinating office at CHaRT for electronic data entry. The data to be collected include data required to complete randomisation; intra- and postoperative.

iv. Return all study documentation to the Study Office (CHaRT, Aberdeen) for archive.

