### Data collection and processing

Follow-up will continue for six weeks from the date of operation. Clinical data will be collected on participants who will need to be followed-up in clinic, as part of their treatment plan.

Participants will be assessed pre-operatively to confirm eligibility and peri-operative data collected. Patient reported outcomes (PROs) will be collected by diary completed on days one to seven following surgery and by postal questionnaires at six weeks post-surgery. The components of participant follow-up are shown in the Table 1.

**Table 1 T1:** Source and timing of measures

**Outcome measures**	**Source**	**Timing**		
		**Peri- operative**	**Days one to seven diary**	**Six weeks**
BMI, ASA grade	Case Report Form (CRF)	▲		
Duration of operation, intra-operative complication rates, conversion rates, surgeon’s perception of single port approach	CRF	▲		
Intervention received	CRF	▲		
Body Image Questionnaire (BIQ) [20]	Participant Questionnaire (PQ)			▲
Hospital Experience Questionnaire (HEQ) [20]	PQ			▲
Pain Numerical Rating Scale (NRS)	PQ		▲	▲
Use of analgesics	CRF and PQ	▲	▲	▲
Time to return to usual activities	PQ			▲
Hospital re-admissions	CRF and PQ			▲
Complications (for example, infection, port-site hernia)	CRF and PQ	▲		▲

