### Reporting responsibilities of the CI

The Chief Investigator (CI) or deputy will be automatically notified of all SAEs. If, in the opinion of the local surgeon and the CI, the event is confirmed as being related and unexpected, the CI will submit a report to the main REC and the study sponsors within 15 days of the CI becoming aware of it.

As the trial arm to which participants are allocated cannot be blind to the operating surgeons or theatre staff after randomisation has occurred, unblinding is not an issue in this trial. A record of the operative procedures actually carried out will be available in the medical notes if required clinically.

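### Comparing only re-admissions judged related makes an otherwise objective outcome depend on a causal judgement that clinicians who know the allocation could make; all-cause re-admission avoids this at little cost (minor)

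*Protocol article*

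**What the plan says.** All references are to the protocol article.

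- **Clinical outcomes** lists "related hospital re-admission rates up to six weeks". Reoperation, in the same list, carries no relatedness condition.
- **Data collection and processing, Table 1** has a row labelled "Hospital re-admissions", without qualification. Its sources are the case report form (CRF) and the participant questionnaire, at six weeks.
- **Subsequent tasks** has the consultant or a team member "Complete case report forms (CRFs) as appropriate and either enter the data directly onto the SCARLESS website" or forward paper copies. The same people are to "Inform the ward and theatre staff as appropriate of the participant’s study participation and intervention allocation".
- **Reporting responsibilities of the CI** says that the allocation "cannot be blind to the operating surgeons or theatre staff after randomisation has occurred". It also contains the only judgement of relatedness by named roles. This serves expedited reporting of serious adverse events and applies if "in the opinion of the local surgeon and the CI, the event is confirmed as being related and unexpected".
- **Concealment of group allocation to participants** says: "The feasibility of concealing group allocation from the participants and the ward staff will be investigated". Blinding of participants is to be attempted with dressings.
- **Procedure for reporting untoward and related serious adverse events** limits these events to those resulting from the appendicectomy treatment, readmission included, but records deaths from any cause.

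**The concern.** Whether a patient was re-admitted within six weeks is close to a matter of fact. Whether the re-admission was related to the operation is an opinion. The outcome list makes the compared event depend on that opinion, in a trial of a new technique where surgeons and theatre staff know which operation was done.

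If clinicians attribute re-admissions to the new technique more readily than to the standard one, or less readily, the two related rates will differ even when the true re-admission rates are equal. The direction cannot be predicted.

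The adverse-event stream would not catch what is lost. A re-admission judged unrelated leaves the clinical outcome and also falls outside the serious adverse event definition, which is itself limited to events resulting from treatment. The study is meant to give preliminary results and to inform the choice of outcomes for a larger trial, so a weak definition could be carried forward.

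**Working it through.** **1. The plan's own figure.** The only powered quantity concerns patient-reported measures: 80 participants, effect size 0.65, two-sided 5%, 80% power. A two-sample t-test calculation (noncentral t) needs 39 per arm, 78 in total, and gives power 0.819 at 40 per arm. The figure is reproduced. It does not concern re-admission, and nothing below alters it.

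**2. The text, side by side.**

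| Question | What the article gives |
|---|---|
| What is compared? | Related re-admissions only |
| What is listed for collection? | Re-admissions, unqualified, from CRF and questionnaire |
| Who decides relatedness for this outcome? | Not stated |
| Who completes CRFs? | The consultant or a team member |
| Who knows the allocation? | Surgeons and theatre staff; ward staff may be told, although concealment from them is also to be investigated |
| Is the relatedness judgement shielded from the allocation? | Nothing described |

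The restriction is stated. That the judgement would be made with knowledge of the allocation is an inference from the other rows.

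**3. Illustration of size.** The inputs are 40 per arm ("A sample of 80 participants recruited is anticipated over the seven-month recruitment phase", randomised in equal proportion), an *assumed* true all-cause rate p that is the same in both arms, and *assumed* fractions a₁ and a₀ of re-admissions called related. The documents give neither p nor a₁ and a₀.

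- False difference = p × (a₁ − a₀)
- SE = √[p₁(1 − p₁)/40 + p₀(1 − p₀)/40], with p₁ = p·a₁ and p₀ = p·a₀

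Worked case, p = 10%, 90% v 50%: the rates become 9% and 5%. The difference is 0.10 × 0.40 = 4 points. SE = √[(0.0819 + 0.0475)/40] = √0.003235 = 5.7 points. The ratio is 4/5.7 = 0.70.

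| True rate, both arms | Called related | Resulting rates | False difference | SE | Difference/SE |
|---|---|---|---|---|---|
| 5% | 90% v 70% | 4.5% v 3.5% | 1 point | 4.4 | 0.23 |
| 5% | 90% v 50% | 4.5% v 2.5% | 2 points | 4.1 | 0.49 |
| 10% | 80% v 60% | 8% v 6% | 2 points | 5.7 | 0.35 |
| 10% | 90% v 50% | 9% v 5% | 4 points | 5.7 | 0.70 |
| 15% | 90% v 70% | 13.5% v 10.5% | 3 points | 7.3 | 0.41 |
| 15% | 90% v 50% | 13.5% v 7.5% | 6 points | 6.8 | 0.88 |
| 15% | 100% v 50% | 15% v 7.5% | 7.5 points | 7.0 | 1.07 |

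The expected all-cause difference is zero in every row.

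**4. The same in patients.** At 10% there are 4 re-admissions per arm. Compared as 4/40 v 4/40, the difference is 0, with a Newcombe 95% interval of −14.4 to 14.4 points. If two of the four in one arm are called unrelated, the comparison becomes 4/40 v 2/40. The Wilson limits are 4.0% to 23.0% and 1.4% to 16.5%, the difference is 5 points, and the Newcombe interval is −8.0 to 18.5 points. The estimate moves and the interval still includes zero.

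**5. Cost of the alternative.** Suppose 10% are re-admitted in each arm and 80% of these are related in both. The SE of the related difference is √(2 × 0.08 × 0.92/40) = 6.1 points. For all-cause it is √(2 × 0.10 × 0.90/40) = 6.7 points. Incidental admissions that are equal in both arms leave the absolute difference unchanged.

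**The case against.** Three stronger readings are tempting, and the documents do not support them.

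- *The article gives two conflicting definitions.* It does not. Table 1 shows the source and timing of measures in short labels, and the outcome list says what is compared. Deriving a subset from collected data is ordinary practice.
- *Unblinded operators will judge relatedness, with no blinded assessment planned.* The article does not say who judges it for this outcome. CRFs are completed by the consultant or a team member, who need not be the operator. The judgement by the local surgeon and the Chief Investigator concerns expedited reporting. A definition or a blinded procedure may exist in the full protocol or analysis plan, which are not shown, and its absence from an article is no fault.
- *The comparison is biased.* Nothing shows differential attribution. The fractions used above are assumptions, and 90% v 50% is a severe one.

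Other objections carry weight. Counting related re-admissions is a defensible choice because it targets consequences of the operation. All-cause re-admission is not wholly immune either, since the decision to re-admit can be made by someone who knows the allocation. Re-admission is also not the only fairly objective clinical outcome: reoperation, conversion and duration of operation are listed too.

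These objections lower the importance of the point but do not remove it. It rests on a restriction that the article itself states, not on a missing detail. Even a well-defined relatedness rule adds a judgement that the all-cause count does not need.

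**Conclusion.** The point holds as a minor improvement. The stated restriction makes the re-admission comparison depend on a causal judgement, and the article describes nothing that shields that judgement from knowledge of the allocation. Differential attribution is therefore possible, in either direction.

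Its size cannot be derived from the documents. On assumed true rates of 5% to 15% with 40 per arm, the false difference stays below one standard error for splits up to 90% v 50%. It only just exceeds one in the extreme case of 100% v 50% at 15%. With a handful of events in a non-primary, unpowered outcome, this could shift a point estimate by a patient or two, but no main conclusion of the study would turn on it. The primary outcomes, the feasibility measures and the sample size are unaffected.

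**What to change.** In Clinical outcomes, make the compared measure all-cause hospital re-admission up to six weeks by allocated arm, from the CRF and questionnaire data that Table 1 already lists. Report related re-admissions alongside as a descriptive subset with the reason for each. If a rule for relatedness exists elsewhere, a reference to it would suffice. Where practicable, the label should be assigned without sight of the allocation.

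The cost is a small wording change and one more row in the results table. No new data item is needed in Table 1, and no stated figure changes. The downside is slight extra noise from incidental admissions, in the example above an SE of 6.7 instead of 6.1 points.

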#### Feasibility measures

Feasibility measures include eligible patients per month; proportion formally considered for trial entry; proportion randomised (and reasons why not); proportion who are unaware of their received intervention at 24 hours; proportion of those recruited with complete data set at six weeks; surgeon’s perception of SPILS approach and the suitability of available equipment.

#### Resource use

Resource use will be limited to duration of operative procedure, theatre time and use of disposable instruments.

### Statistical analyses

For feasibility measures, such as the proportion of eligible patients who consent to randomisation, the frequency and corresponding 95% confidence interval will be calculated. Patient-reported and clinical measures will be summarised using appropriate summary measures (for example, frequency or mean and standard deviation) for each treatment group. The treatment groups will be compared at the two-sided 5% significance level. BIQ and pain NRS (area under the curve over a seven-day period) will be analysed using an independent *t*-test. Other outcomes will be assessed using standard statistical methods as appropriate, for example, comparison of proportions Newcombe’s CI method [21] or chi-squared test for trend [22], and independent *t*-test for binary and continuous outcomes respectively. Corresponding 95% confidence intervals will also be calculated. A single principal analysis is anticipated at the end of the study following intention to treat principle (grouped according to allocation). No imputation for missing data will be carried out. All analyses will be conducted using Stata 12 [23].

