### Randomisation and allocation

Participants will be recruited from a single centre, Aberdeen Royal Infirmary (UK). Following consent and collection of baseline data, the local consultant/designated team member will randomise the patient.

Participants will be randomised to one of the two study groups in equal proportion using the randomisation application at the trial office at the Centre for Healthcare and Randomised Trials (CHaRT), Aberdeen. Randomisation will be stratified by gender and computer generated permuted blocks of varying size used within each stratum. This randomisation application will be available 24 hours a day, seven days a week as an Interactive Voice Response (IVR) telephone system. Due to the acute nature of the admission to surgery and potential difficulty in tracking patients, date of birth will also be recorded in the randomisation process and available, if necessary, for use in addition to the study number to identify patients. The date of birth will not be openly available.

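### The general 95% confidence-interval rule for feasibility measures also covers surgeon-reported ratings, where repeat ratings by the same surgeon would make an interval that treats operations as independent too narrow

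*Protocol article*

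**What the plan says.** The Feasibility measures section of the protocol article ends its list, which otherwise consists of patient counts and proportions, with "surgeon’s perception of SPILS approach and the suitability of available equipment". The Statistical analyses section then sets one rule: "For feasibility measures, such as the proportion of eligible patients who consent to randomisation, the frequency and corresponding 95% confidence interval will be calculated". The example it gives is a patient-level proportion, and no separate method is named for the surgeon-reported items.

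Table 1, under Data collection and processing, places perception in a row filled from the case report form (CRF) at the peri-operative time point: "Duration of operation, intra-operative complication rates, conversion rates, surgeon’s perception of single port approach". Equipment suitability has no row of its own.

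Under Randomisation and allocation, "Participants will be recruited from a single centre", with equal allocation. The Sample size section expects 80 participants and gives a precision statement restricted to binary items: "Binary feasibility measures are likely to be estimated with a (one-group) confidence interval of between 10 and 20" per cent. The Trial interventions section has operations delivered or supervised by a surgeon with expertise in the technique.

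**The concern.** A patient's decision to be randomised can reasonably be treated as independent of another patient's. A surgeon's view of a technique is different, because much of it belongs to the surgeon and carries over from one operation to the next. If one surgeon rates ten operations, those ten ratings hold less information than ten ratings from ten surgeons.

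The rule makes no such distinction. Followed literally, the surgeon items would be given an interval whose sample size is the number of operations. Surgeon perception is part of a stated objective of the study, and the Background says that the results are meant to inform a large multicentre trial. An interval that looks more precise than it is would overstate how much has been learned about acceptability to surgeons.

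**Working it through.** **Inputs from the protocol article.** 80 participants allocated equally give 80/2 = 40 SPILS operations. I take perception of SPILS to be rated in that arm only; this follows from the subject of the item but is not written. There is one centre. One rating per operation is implied by the row of Table 1, not written.

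**Inputs that are assumed.** Number of rating surgeons k = 2 to 10, with equal caseloads m = 40/k; ICC 0.05 to 0.5; a yes/no item with 70% favourable. The article gives none of these.

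**The plan's own precision figure.** With n = 80, the full width of a Wilson 95% interval is 10.2 points at a proportion of 0.05, 19.7 at 0.3 and 21.4 at 0.5. The stated 10 to 20% is thus roughly reproduced as a full width for a binary item observed in all 80 participants. With n = 40 the Wilson full width is 15.1 points at 0.05 and 29.6 at 0.5, before any clustering.

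**Effect of repeat raters.** Design effect DE = 1 + (m − 1) × ICC. Effective sample size = 40/DE. Half-width = 1.96 × √(p(1 − p)/n).

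Worked case, k = 4 and ICC 0.3:
- m = 40/4 = 10
- DE = 1 + 9 × 0.3 = 3.7
- effective n = 40/3.7 = 10.8
- half-width treating operations as independent: 1.96 × √(0.21/40) = 0.142, or 14 points
- half-width allowing for clustering: 1.96 × √(0.21/10.8) = 0.273, or 27 points

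**Coverage of the interval that ignores surgeons.** I simulated beta-binomial ratings (70% favourable, 40 operations, 100,000 runs per case) and computed the Wilson 95% interval with n = 40. The last column is the approximation 2Φ(1.96/√DE) − 1.

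| Surgeons | ICC | DE | Effective n | Simulated coverage | Approximation |
|---|---|---|---|---|---|
| 10 | 0 | 1.00 | 40.0 | 94.5% | 95.0% |
| 10 | 0.05 | 1.15 | 34.8 | 92.6% | 93.2% |
| 8 | 0.1 | 1.40 | 28.6 | 89.5% | 90.2% |
| 5 | 0.1 | 1.70 | 23.5 | 85.7% | 86.7% |
| 4 | 0.3 | 3.70 | 10.8 | 66.2% | 69.2% |
| 2 | 0.5 | 10.50 | 3.8 | 34.8% | 45.5% |

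The row with ICC 0 shows that the loss comes from clustering and not from the interval method. The lowest figure depends on the assumed proportion: with 50% favourable, the case of 2 surgeons and ICC 0.5 has a simulated coverage of 45.3%.

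**The case against.** The strongest reply is that the article fixes less than the concern needs. The sentence in the Statistical analyses section does not say that every feasibility measure gets a binomial interval, its example is a patient-level proportion, and it names no interval method, so a clustered interval is not excluded. The item's scale is not given and could be ordinal or free text. The precision statement in the Sample size section is confined to binary measures. The number of surgeons is not stated, and since operations may be supervised, trainees may also be raters, which would enlarge the pool. If the aim is only to describe the operations done by this hospital's own surgeons, inflation for sampling of surgeons does not apply. The detail may also be settled in an analysis plan that is not shown. No test, threshold or progression rule uses this interval.

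Most of this stands, and it limits the point. A reader might infer that a small group of surgeons certainly does the rating, that the interval is certainly far too narrow, or that the 10 to 20% precision figure was meant for this item. The documents support none of these: they give no number of surgeons, no correlation and no scale, and they restrict the precision figure to binary items.

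What remains is that the surgeon items are listed as feasibility measures and the rule for feasibility measures is stated without exception. Among about 40 operations at one hospital, repeat raters are very probable, and some positive correlation within rater is to be expected. An ordinal item would meet the same difficulty in any interval on its category frequencies. Since the study is meant to inform a multicentre trial, surgeons beyond this hospital are the natural target of inference.

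**Conclusion.** The point holds in conditional form and is minor. The article puts surgeon perception and equipment suitability under the same frequency-and-interval rule as patient-level proportions. An interval that treats operations as independent would be too narrow to the extent that ratings correlate within surgeon. Over the assumed ranges the effect goes from negligible to large: coverage of about 93% with 10 surgeons and ICC 0.05, about 35% with 2 surgeons and ICC 0.5, and no loss at ICC 0. These figures rest on 40 SPILS ratings, equal caseloads and a binary item with 70% favourable. The effect is confined to these descriptive surgeon-reported items; the primary outcomes, the group comparisons and the sample size are not touched.

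**What to change.** In the Statistical analyses section, exempt surgeon-reported items (perception of SPILS and suitability of equipment) from the general feasibility interval. State the number of rating surgeons and report the ratings descriptively by surgeon, using operator identity; add an anonymous surgeon code if the CRF does not already hold one. Give an interval only if it accounts for clustering by surgeon, for example one built from surgeon-level summaries. If there are too few surgeons for that, give frequencies without a 95% confidence interval.

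The cost is a short change of wording and possibly one CRF field. The downside is that the interval becomes wider or is dropped.

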### Outcome measures

#### Primary effectiveness outcomes

The patient reported outcome measure is the patient reported cosmesis and body image using the Body Image Questionnaire (BIQ) [20] at six weeks; participants will be asked five questions about their body image using the scale on a 4-point Likert scale of:’no, not at all’; ‘a little bit’; ‘quite a bit’; ‘yes, extremely’, two questions about their incisional scar to be rated on a scale of 1 (very unsatisfied/revolting) to 7 (very satisfied/beautiful), one further question regarding the scar using a 10-point Numerical Rating Scale (NRS), and a question regarding confidence on a 10-point numerical scale from 1 (not very confident) to 10 (very confident). The clinical outcome of severity of pain (Pain NRS) will be measured using a pain scale (scale from 0 (no pain) to 10 (worst imaginable pain)) at one to seven days.

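### Two unranked primary outcomes are each tested at 5% with no adjustment, so an effectiveness claim resting on either one carries up to a 9.75% false-positive risk, and the power figure covers only one such test

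*Protocol article*

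**What the plan says.** The outcome section has a plural heading, "Primary effectiveness outcomes", and two entries. The first is cosmesis and body image by BIQ at six weeks. The second is introduced with "The clinical outcome of severity of pain (Pain NRS) will be measured using a pain scale" and is collected on days one to seven. The section does not rank them or say whether one or both must be positive.

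The Statistical analyses section states: "The treatment groups will be compared at the two-sided 5% significance level". It names an independent t-test for BIQ and for the seven-day area under the pain curve, promises 95% confidence intervals, and foresees one principal analysis by allocated group. It mentions no multiplicity procedure.

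The Sample size section gives "A sample of 80 participants recruited is anticipated over the seven-month recruitment phase". Using the full, undivided 5% level (two-sided), it then states what a standardised difference this sample could pick up: "of 0.65 to be detected with 80% power for patient reported measures, such as the Body Image Questionnaire". Allocation is 1:1: "Participants will be randomised to one of the two study groups in equal proportion".

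**The concern.** Where two outcomes are both primary and nothing says how they combine, the report can claim effectiveness if BIQ differs, if pain differs, or if both do. Each test has its own 5% chance of a false positive, so the chance that at least one fires when neither outcome truly differs exceeds 5%.

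The power figure has the matching gap. It describes a single 5% test of a patient-reported measure, with BIQ as the example. It does not say what the trial can detect once the 5% is shared between two primaries, and the outcome section calls the second primary a clinical outcome.

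At stake is how a single positive primary result would be read. The Background says that objective data are needed during the introduction of the technique to inform its further adoption. A significant result on one of two unranked primaries could be taken as 5% evidence when it is weaker than that.

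**Working it through.** **Inputs from the protocol article**
- 80 participants (Sample size), allocated 1:1 (Randomisation and allocation), so n = 40 per arm. This assumes that everyone recruited is analysed.
- Two-sided significance level 0.05 (Sample size; Statistical analyses).
- d = 0.65 with 80% power (Sample size).
- Two primary tests: BIQ and pain area under the curve (Primary effectiveness outcomes; Statistical analyses).

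**Step 1. Reproduce the stated power.** The noncentrality is d × √(n/2) = 0.65 × √20 = 2.907.
- Normal approximation: Φ(2.907 − 1.960) = Φ(0.947) = 82.8%.
- Two-sample t-test (noncentral t): 81.9%.
- Effect detectable with 80% power (t-test): d = 0.634.

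The stated 80% at d = 0.65 is therefore reproduced, for one test at 5%.

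**Step 2. False-positive risk over two tests.** With no true difference on either outcome and independent tests:

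1 − (1 − 0.05)² = 1 − 0.9025 = 9.75%.

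Simulation with correlated normal test statistics (1,000,000 draws) gives 9.1% at correlation 0.5 and 8.3% at 0.7. The documents give no correlation, so these values are assumptions. Correlation lowers the risk only modestly.

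**Step 3. Power when 5% is shared.** At 0.05/2 = 0.025 per test, the two-sided critical value is 2.241.
- Normal approximation: Φ(2.907 − 2.241) = Φ(0.666) = 74.7%.
- t-test: 73.2%.
- Effect detectable with 80% power, 40 per arm (t-test): d = 0.70.
- Holding 80% power at d = 0.65 would take 46.3, so 47 per arm, or 94 in total (t-test).

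Holm's procedure compares the smaller p-value with 0.025 and, if that is significant, the larger with 0.05. The figures at 0.025 are therefore its conservative case.

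**Step 4. Power if both must be significant.** If each true effect is d = 0.65 and the tests are independent: 0.819 × 0.819 = 67%. This is also the power for pain under a fixed sequence that starts with BIQ.

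**The case against.** The strongest reply is that the protocol never says either result alone counts as success. If both were required, the false-positive risk would not be inflated, and one patient-reported and one clinical outcome can be read as two separate questions. That stands as a condition on the 9.75%. But no both-required rule is written either, so the either-or reading remains open to whoever reports the trial.

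A second reply is that this is preliminary work. The Background calls for a feasibility study to inform a larger trial, the sample size is anticipated recruitment rather than a formal calculation, and confidence intervals are promised. That softens the point. It does not remove it, because the same article states an aim of comparing effectiveness, gives a power figure and plans significance tests.

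A third reply is that the power statement is right. It is: it claims 80% for one 5% test and does not claim joint power. The 73.2% arises only once the level is split, which the protocol has not chosen to do.

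A reader might also go further. BIQ combines five body-image items, two scar ratings, and "one further question regarding the scar using a 10-point Numerical Rating Scale (NRS), and a question regarding confidence on a 10-point numerical scale". One might infer that it has no single score, that a raw total would mix unlike scales, or that testing three parts plus pain would take the risk to 18.5% (1 − 0.95⁴). The documents do not support this. The Statistical analyses section plans one t-test for BIQ and no passage states a split or a raw sum. Scoring may be set out in the cited instrument or in an analysis plan not shown.

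**Conclusion.** The point holds for the two tests that the article actually plans. With BIQ and seven-day pain both primary and each tested at 5%, the chance of at least one false positive is up to 9.75%, or about 8 to 9% at correlations of 0.5 to 0.7. This rests on two assumptions: that neither outcome truly differs, and that either result alone could support an effectiveness claim.

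The sample size statement is not an error. It is incomplete for two primaries. With 40 analysed per arm and the level split, power at d = 0.65 is about 73% rather than 82%, and the detectable effect is about 0.70.

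This is a moderate point: the protocol leaves open which result carries the effectiveness claim, and that should be settled before the data are seen.

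**What to change.** Choose one of the following.

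1. **Keep both as primary.** In Statistical analyses, state that Holm's procedure is applied across the BIQ test and the pain area-under-the-curve test. In Sample size, restate the detectable effect as about d = 0.70 with 80% power and 40 per arm, noting that power at d = 0.65 is about 73% at the 2.5% level. The cost is a slightly less favourable detectable effect at the same sample size.

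2. **Fixed sequence.** Test BIQ at 5%, and test pain at 5% only if BIQ is significant. BIQ goes first because it is the measure named in the power statement, and that statement then stands unchanged for it. The cost is that pain cannot be claimed on its own if BIQ is not significant.

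Either change takes a sentence or two. BIQ can stay primary as the article names it, covering both cosmesis and body image; there is no need to narrow it to its scar items.
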